## Abstract

Sedentary lifestyles have become a social problem, mainly among women. A sedentary lifestyle has been associated with poorer health in this population, negatively affecting physical and mental health. Physical exercise, in particular high-intensity interval training (HIIT), has been shown to be a neuroprotective tool. The present study provides a protocol design for a parallel-group Randomized Controlled Trial (RCT), whose aim will be to compare the effect of two physical interventions, HIIT and physical activity (increasing daily steps), on Insulin Growth Factor-1 (saliva IGF-1 concentrations), executive functions, quality of life, body composition, physical fitness, and physical activity in young sedentary women. At least 77 women will be recruited and randomly assigned to either a HIIT group (12-week exercise HIIT intervention, 3 sessions/week), the HIIT + PA group (12-week exercise HIIT intervention, 3 sessions/week, plus 10,000 steps/day), or a control group (usual care). The primary outcome measure will the chronic change in IGF-1 concentration levels measured in saliva. Secondary outcome measures will be: (i) executive functions; (ii) body composition; (iii) physical fitness; (iv) physical activity; and (v) quality of life. All outcomes will be assessed at the beginning of the study, after the intervention, and after three months of follow-up. After this intervention, we will be able to determine whether HIIT together with increased physical activity could be more effective than HIIT alone in IGF-1 stimulation. Furthermore, by comparing both intervention groups, we will be able to determine the differential effects on numerous health-related variables. Consequently, the conclusions of this study could help better understand the effects of a training program on IGF-1 concentration levels and executive functions. In addition, various strategies could be proposed through physical exercise to improve cognition in this age group, as well as to improve the health status of this sedentary population.

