### 2.3. Sample Size

The sample size will be calculated in an a priori analysis (G*Power V.3.1.9.6) on the basis of the change in IGF-1 levels with reference to the results of the Antonelli et al. study [22]. This study will require a sample size (for each group) of 37 (41, assuming a subject loss of 10%). This is for an alpha = 95%, a statistical power of 80% and a precision (d) of 5.23. According to the objectives and design of the study, and to form three groups of subjects, the subjects will be randomly distributed into two experimental groups (HIIT and HIIT + PA) and a control group (CG). All groups will be made up of healthy female university students who are all sedentary and inactive and willing to participate in the study.

To attain this number of female university students, recruitment will be carried out through online dissemination via the institutional website of the University of Seville, e-mails and social networks. Once all female students with interest in participation are registered, different information sessions will be scheduled prior to the start, during which the inclusion and exclusion criteria will be applied. In this way, a greater homogeneity of the sample will be obtained, and it will be possible to achieve a reduction of possible biases.

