### 2.4. Randomization and Blinding

After baseline assessments, all participants will be randomly assigned to the HIIT intervention (HIIT), the HIIT intervention plus 10,000 steps per day (HIIT + PA), or the control group (CG). A simple computer-generated randomization sequence (www.randomizer.org) will be created prior to enrolling participants to assign them to the HIIT group, HIIT+PA, or the control group. While participants will be aware of their group allocation, outcome assessors and data analysts will be blinded to the allocation.

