### 2.7. Statistical Analysis

Once data are obtained in the three research groups (HIIT, HIIT + PA, and CG) they will be compared at baseline, after 12 weeks of intervention, and three months after the end of the training program. Frequency tables will be obtained for the sociodemographic variables and means and standard deviations for the quantitative variables. The effects of the intervention on the primary and secondary outcomes will be evaluated with repeated measured analysis. The effect size (95% confidence interval), percentage of change, and statistical significance will be reported for each outcome with regards to the main group (between-subjects) time (within-subjects) and their interaction (group × time) effects.

Finally, various correlation analyses between the different variables will be carried out using Spearman’s Rho.

All data will be processed with the SPSS v.26 statistical program, establishing a confidence interval of 95% and estimating a significance level of *p* equal to or less than 0.05.

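### The abstract's minimum of 77 women is below the 111 evaluable (123 recruited) that section 2.3 implies for three groups, and nothing reconciles the two

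*Protocol article*

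**What the plan says.** Abstract: "At least 77 women will be recruited and randomly assigned to either a HIIT group", the HIIT + PA group or the control group. The figure is a total over three arms and is worded as a minimum.

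Section 2.3 (Sample Size): "This study will require a sample size (for each group) of 37 (41, assuming a subject loss of 10" per cent). The calculation was done "on the basis of the change in IGF-1 levels with reference to the results of" a cited study. Its other inputs are given as follows: "This is for an alpha = 95%, a statistical power of 80% and a precision (d) of 5.23". The same paragraph says that, "to form three groups of subjects, the subjects will be randomly distributed into two experimental groups (HIIT and HIIT + PA) and a control group".

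Section 2.4 (Randomization and Blinding) specifies simple randomization to the three groups and states no allocation ratio. Section 2.7 (Statistical Analysis) works at "estimating a significance level of *p* equal to or less than 0.05" and does not say whether tests are one- or two-sided.

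**The concern.** Section 2.3 gives its number per group, so 37 and 41 cannot be read as totals. With three groups they imply 111 and 123, yet the abstract sets its minimum at 77. Two groups would not give 77 either (2 × 37 = 74, 2 × 41 = 82), and no other part of the visible text produces it.

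The sample size is the commitment behind the stated 80% power. The main hypothesis (section 1) compares HIIT + PA with HIIT alone, two active arms between which a modest difference is plausible. A team that treated the abstract's floor as sufficient would make that comparison with roughly two thirds of the women section 2.3 calls for, while the article still quoted 80%.

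**Working it through.** **Inputs.** Abstract: at least 77 in total. Section 2.3: 37 per group, 41 with 10% loss, three groups, power 80%, alpha printed as 95%, d = 5.23 with no unit. Section 2.7: significance level 0.05. Assumptions: alpha is 0.05 (95% being the confidence level), arms are equal, and the target is a pairwise comparison of means.

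**1. Can 37 be reproduced?** No. The usual formula is n = 2(z₀.₉₇₅ + z₀.₈₀)² / (difference/SD)² per group, and section 2.3 gives no SD. If 5.23 is read as a standardized effect, n = 2 × 2.80² / 5.23² = 0.57, or 1 per group, so it is not that. If it is a raw difference, 37 per group implies an SD of about 8.0 (normal approximation) or 7.9 (t test). The article gives no figure to check this against.

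**2. The loss step.** 37 × 1.10 = 40.7, rounded up to 41, which matches section 2.3. Dividing by the retained fraction gives 37/0.9 = 41.1, or 42. The difference is one woman per arm.

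**3. Totals.**

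| | Per group | Three groups | 77 as a share |
|---|---|---|---|
| Evaluable | 37 | 111 | 69% (34 fewer) |
| Recruited, as in section 2.3 | 41 | 123 | 63% (46 fewer) |
| Recruited, using 37/0.9 | 42 | 126 | 61% (49 fewer) |

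**4. Arm size at the floor.** 77/3 = 25.7 per arm. After 10% loss, 25.7 × 0.9 = 23.1.

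**5. Power at the floor, if 37 per group gives exactly 80%.** Solving for the standardized effect at n = 37 and holding it fixed:

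| Test at 0.05 | Effect at which 37 per group gives 80% | Power, 77 with no loss | Power, 77 after 10% loss |
|---|---|---|---|
| Two-sample t, two-sided | 0.660 | 64.0% | 59.3% |
| Two-sample, normal approximation, two-sided | 0.651 | 64.6% | 60.0% |
| Two-sample t, one-sided | 0.584 | 66.2% | 62.1% |
| Three-group one-way ANOVA | f = 0.299 | 62.8% | 57.5% (69 women) |

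Check on the normal row: 0.651 × √(25.7/2) − 1.96 = 0.37, and Φ(0.37) is about 0.65.

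**6. Detectable difference at 80% power.** It scales with √(37/n): √(37/25.7) = 1.20 and √(37/23.1) = 1.27, so it is 20% to 27% larger than planned.

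**The case against.** The strongest reply is that 77 is only a floor. Recruiting 123 women would satisfy the abstract and section 2.3 together, section 2.3 is the operative text, and its recruitment paragraph refers to reaching its own number. That stands as far as it goes. A reader might infer that the two figures are mutually exclusive, or that recruitment will stop at 77, and the article says neither. But a minimum is the smallest number the trial presents as acceptable, and this one is below the 111 evaluable women that section 2.3 says are required.

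The second reply is that the power figures are back-solved. That also stands. They take 37 as exactly right and use a two-sample test or a one-way ANOVA, whereas section 2.7 plans a repeated-measures analysis with a group-by-time interaction. A reader might infer that the trial is simply underpowered at about 60%. The documents do not support that unconditionally: if 37 is the figure in error, power at 77 is unknown.

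Two further inferences should be avoided. The origin of 77 cannot be recovered from the text. That it does not divide by three shows nothing, since simple randomization does not produce equal arms. Nor would a null result at 77 be worthless, because section 2.7 plans 95% confidence intervals, which would still be informative though wider.

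The participant flow diagram is not reproduced in the text at hand and may carry group numbers. Even if it does, the two printed figures would still disagree.

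**Conclusion.** The inconsistency is established from the abstract and section 2.3 alone: a floor of 77 against 111 evaluable and 123 recruited, a gap of 46 women (37%) on recruitment. The article does not show which figure is intended.

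The consequence for power is conditional. If 37 per group is what gives 80%, then 77 in total gives less, whatever the SD. The size of the loss (about 64% before and 59% after 10% loss, or 63% and 58% by three-group ANOVA) rests on equal arms, alpha of 0.05, two-sided testing for the pairwise figures, and 37 being correct. Section 2.3 does not give enough to verify that last point. The conflict needs correcting because it concerns the trial's basic size commitment and both figures appear in the same article.

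**What to change.** State one total everywhere.

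- **If section 2.3 is right:** replace 77 in the abstract with 123 recruited and 111 evaluable, or 126 recruited if loss is applied as 37/0.9. This costs one corrected figure and adds nothing to what section 2.3 already commits to.
- **If 77 is the real target:** restate section 2.3 with the per-group number (about 26 recruited, about 23 evaluable) and the power that 77 delivers. Compute that power from a stated effect, SD, test and alpha; do not carry over the back-solved percentages above. Under the present planning assumption it would be about 59% to 64%, so the cost is disclosing less favourable power than 80%.

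In either case section 2.3 should give the SD, the unit of 5.23, the test and its sidedness, and should correct the printed alpha, so that the per-group number can be reproduced.

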## 1. Introduction

A sedentary lifestyle, understood a lifestyle of activities that require minimal body movement [1]; is one of the main factors responsible for chronic diseases in adults. Focusing on the most common age group among university students, i.e., 18 to 25 years of age, there is a significant decrease in physical exercise at this educational stage [2]. This means that the physical exercise recommendations set out by the WHO [3] are not met. Furthermore, if we compare the sexes, women are found to be 8% more inactive than men [4]. 

For these reasons, this protocol study is proposed because it is interesting to investigate the possible health-related factors involved, such as quality of life, physical condition, and mental health. It is well known that sedentary behavior over time is correlated with a greater loss of muscle mass, an increase in fat mass [5], body fat percent and fat mass index [6], together with social and psychological changes. These conditions can have a premature negative impact on cognition, with deficits in executive functions and even a reduction in the concentration of key neurotrophic factors in the brain. In addition to this problem, COVID-19 has increased sedentary behavior in this population [7], with as many as 1.4 billon adults failing to meet the minimum recommendations proposed by the WHO [8]. This pandemic situation has also generated changes in the quality of life of this population, showing a worse perception of their general health and mental health status [9]. 

Young women are at high risk of being inactive and sedentary, which can alter their emotional state through increased anxiety, stress, reduced cognitive and executive function, and even increased all-cause mortality. In addition, the young adult period is a critical time for consolidating neural and synaptic pathways [10]. Therefore, reducing the time spent in sedentary positions may be fundamental for a good consolidation of cognitive abilities and, more specifically, of executive functions [11]. In this way, this strategy can lead to medium- to long-term prevention of cognitive impairment.

Physical exercise has proven to be a useful strategy to improve performance in executive functions in adults [12]. This positive impact may be due to its effect on plasticity and neuronal growth. In fact, physical exercise leads to increased cerebral blood flow, increased neurogenesis stimulation, optimized synaptic interconnections, and increased generation of neurotrophic factors such as IGF-1 [13]. IGF-1 has been shown to be a potent facilitator of brain plasticity in young adults. Thus, a higher concentration of IGF-1 may be conducive to higher brain performance and better cognition [14].

Despite these effects of physical exercise on executive functions and IGF-1 concentrations, it is known that, depending on the type of physical exercise performed, its effect may lead to different results. However, the intensity variable appears to be an important element in generating greater stimulation of IGF-1 [15]. Low–moderate intensity exercise has shown some chronic benefits in both IGF-1 concentration and executive functioning. In contrast, high-intensity exercise has shown greater performance for both variables. 

In recent years, due to the significant increase in the practice of HIIT in society [16], there has been a high level of interest in knowing its effect on different health variables, such as physical and psychological fitness [17], cardiometabolic parameters such as glycemic control, and even cognitive functions [15]. These studies show that HIIT is an efficient strategy to improve all these health-related variables. However, there is little evidence comparing the combination of a HIIT training program with an increase in light physical activity (daily steps) versus performing only the HIIT training program, or analyzing its effect on physical fitness, mental health, and quality of life in the population described.

Therefore, the hypothesis of the study is that a 12-week HIIT program implemented with an increase in daily physical activity (HIIT + PA) enhances to a greater extent executive functions, IGF-1 concentration, physical condition, body composition, and quality of life in sedentary young women than a similar program (HIIT) alone.

For resolve this issue, this plan includes a specific program focused on sedentary university women, with the objective of increasing their levels of physical activity. In this context, we designed an RCT to investigate the effects of a HIIT program versus the same program plus an increase in their daily physical activity on IGF-1 concentrations and executive functions. The purpose of this methodological article is to describe the study design, procedures, and methods that will be used in this research. 

## 2. Materials and Methods

### 2.1. Study Design

The present study is a parallel-group RCT (ClinicalTrials.gov accessed on 30 November 2022. ID: NCT05642169). The research study complies with the Declaration of Helsinki and has been reviewed and approved by the Andalusian Bioethics Committee (IC 1409-N-20). An organizational and participant flow diagram is shown in Figure 1, and the schedule of enrolment, interventions, and assessments is provided in Figure 2. 

### 2.2. Participants and Recruitment Process 

Women will be recruited through online dissemination through the institutional website of the University of Seville, emails, and social networks. A selection of all interested women will be made based on the inclusion and exclusion criterion detailed below (Table 1). Furthermore, they will have to provide their written informed consent before participating in the research, which will be carried out in agreement with the CONSORT statement [18].

### 2.3. Sample Size

The sample size will be calculated in an a priori analysis (G*Power V.3.1.9.6) on the basis of the change in IGF-1 levels with reference to the results of the Antonelli et al. study [22]. This study will require a sample size (for each group) of 37 (41, assuming a subject loss of 10%). This is for an alpha = 95%, a statistical power of 80% and a precision (d) of 5.23. According to the objectives and design of the study, and to form three groups of subjects, the subjects will be randomly distributed into two experimental groups (HIIT and HIIT + PA) and a control group (CG). All groups will be made up of healthy female university students who are all sedentary and inactive and willing to participate in the study.

To attain this number of female university students, recruitment will be carried out through online dissemination via the institutional website of the University of Seville, e-mails and social networks. Once all female students with interest in participation are registered, different information sessions will be scheduled prior to the start, during which the inclusion and exclusion criteria will be applied. In this way, a greater homogeneity of the sample will be obtained, and it will be possible to achieve a reduction of possible biases.

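### The sample-size paragraph misstates alpha and leaves the effect of 5.23 undefined, so 37 per group and its 80% power cannot be verified and are tied to no named comparison

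*Protocol article*

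**What the plan says.** Section 2.3 of the Protocol article says that the size comes from an a priori G*Power calculation, "on the basis of the change in IGF-1 levels with reference to the results of the" cited study. The result reads: "This study will require a sample size (for each group) of 37 (41, assuming a subject loss of 10"%). The inputs follow: "This is for an alpha = 95%, a statistical power of 80% and a precision (d) of 5.23". The women are then divided among HIIT, HIIT + PA and control. The section does not say which two arms the calculation compares, which test it uses, whether it is one- or two-sided, what SD it assumes, or in what unit 5.23 is expressed.

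Section 2.7 sets the test level by "establishing a confidence interval of 95% and estimating a significance level of *p* equal to or less than 0.05", and plans a repeated-measures analysis with group, time and group × time effects.

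The hypothesis at the end of the Introduction is that HIIT + PA improves IGF-1 and the other outcomes more "than a similar program (HIIT) alone". The Abstract frames the IGF-1 question the same way and gives a recruitment minimum of 77 women for the three groups.

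**The concern.** Two of the three printed inputs are faulty as they stand. The first gives a confidence level the name alpha. The second, precision (d), merges two different quantities: precision usually means the half-width of a confidence interval, and d usually means a standardised effect. The two lead to different calculations, and a raw mean difference leads to a third.

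This matters because a stated 80% power is what readers rely on when a primary comparison is not significant. If HIIT + PA and HIIT do not differ on salivary IGF-1, a reader will want to know how large a difference the trial was built to find. From section 2.3 that reader cannot tell what 5.23 measures, how large it is relative to the spread of the data, or whether it refers to adding steps to HIIT, to HIIT against control, or to a change within one group.

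**Working it through.** **Inputs.** From section 2.3: 37 per group, 41 with 10% loss, power 80%, effect 5.23. From section 2.7: level 0.05. Assumed here, because not stated: equal groups, one comparison of two independent means, t test, two-sided unless noted.

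**1. Alpha.** A literal alpha of 0.95, two-sided, has a critical value of z = 0.063, so almost any result would be significant. With d = 5.23 the usual formula then gives 1 per group. The only workable reading is 95% confidence, that is alpha = 0.05, in line with section 2.7.

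**2. 5.23 as a standardised effect.** Noncentral t power with noncentrality d·√(n/2) and 2n − 2 degrees of freedom:

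| n per group | power at d = 5.23 |
|---|---|
| 2 | 75.0% |
| 3 | 99.6% |
| 37 | about 100% |

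This reading needs 3 per group and does not give 37.

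**3. 5.23 as a raw difference.** At n = 37, alpha 0.05 two-sided and 80% power, the t test detects d = 0.660. The implied SD is 5.23 / 0.660 = 7.92. The normal approximation, SD = 5.23 × √(37/2) / (1.960 + 0.842), gives 8.03. One-sided, the t test detects d = 0.584, and the SD is 5.23 / 0.584 = 8.96. So 37 can be reproduced, but only by supplying an SD that the article does not print. The result is sensitive to it:

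| assumed SD | n per group, two-sided t test |
|---|---|
| 7.0 | 30 |
| 7.9 | 37 |
| 9.0 | 48 |
| 10.0 | 59 |

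**4. 5.23 as a 95% confidence-interval half-width.** For one mean, 37 would imply SD = 5.23 × √37 / 1.96 = 16.2. For a difference of two means, SD = 5.23 × √(37/2) / 1.96 = 11.5. Power does not enter such a calculation, so this reading does not fit a sentence that states 80% power.

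**5. What 37 per arm provides.** It gives 80% power for 0.66 SD in one two-sided pairwise contrast at 0.05. As an illustration only: if the gain from adding steps were half of that (0.33 SD, an assumption), power would be 29%.

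**6. Loss and totals.** 37 × 1.1 = 40.7, rounded to 41; 37 / 0.9 = 41.1, which rounds up to 42. The printed 41 is close enough on either convention. The totals are 3 × 37 = 111 and 3 × 41 = 123, against the Abstract's minimum of 77.

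**The case against.** The strongest reply is that the number can be recovered. Section 2.3 speaks of a change in IGF-1 and states a power, which points to a raw difference. An SD near 8 then gives 37, that SD may stand in the cited study, and a condensed article need not print every input. The alpha of 95% is plainly a confidence level under the wrong name, and section 2.7 leaves no doubt about the level used.

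Much of this stands. A reader might infer that the printed inputs cannot produce 37 at all. That goes too far, because the raw-difference reading does produce it, and no arithmetic error is shown. An unprinted SD alone would be a modest matter. But the article does print its inputs: one is wrong, and the other carries a label that, read in the usual way, contradicts the result. Those are misstatements, not details left to a longer document.

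A reader might also infer that the 80% does not apply to HIIT + PA versus HIIT, or that this comparison is underpowered. The documents support neither. Section 2.3 names no contrast, so it excludes none, and other parts of the article describe the aim more broadly as the effect of HIIT on IGF-1. Splitting alpha over three pairwise tests (0.0167 each) would lower power at 0.66 SD to 65%, but the plan makes no such split. The 29% rests on an effect chosen for illustration. Finally, all these figures use a simple two-sample t test, whereas section 2.7 plans a repeated-measures analysis.

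**Conclusion.** The point holds in a limited form. Section 2.3 states alpha wrongly and gives an effect that cannot be a standardised d, since d = 5.23 needs about 3 women per group. The 37 follows if 5.23 is a raw IGF-1 difference with an unstated SD of about 7.9 (two-sided t test; about 9.0 if one-sided). Until that is written down, the 80% power cannot be verified. It is also attributed to no comparison, although the hypothesis and the Abstract make HIIT + PA versus HIIT alone the main question.

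The firm figure is that 37 per arm gives 80% power for 0.66 SD in one two-sided pairwise contrast at 0.05, assuming equal groups and a t test. Nothing here shows that the trial is too small. It shows that the article does not say what the trial is large enough to detect.

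**What to change.** Rewrite the calculation in section 2.3 so that it can be repeated:

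- give alpha as 0.05, two-sided, in agreement with section 2.7;
- define 5.23 as a raw difference in IGF-1, with its unit and the SD used, or correct the figure, and drop the label precision (d);
- name the contrast and the test, and say whether the contrast is HIIT + PA versus HIIT;
- if 37 per arm is kept, state that it gives 80% power for 0.66 SD in one pairwise contrast. Power for a smaller gain from adding steps, such as 29% at 0.33 SD, may be added if it is labelled as an assumption;
- reconcile the resulting total (111, or 123 with losses) with the minimum of 77 in the Abstract.

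The cost is one paragraph and a power statement that may look less favourable. The rewrite itself needs no extra participants or procedures.
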